### Study aims

The aim of our proposed study is to determine the efficacy of a community-led intervention in changing environmental determinants of lifestyle health behaviours by targeting barriers relating to increasing physical activity and healthy eating as defined by community members *themselves*. Information on process and effect size will be used to design a larger controlled trial should the findings be positive.

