### Proposed sample size

Sample size calculations for the independent survey sample are based on Cohen's arcsine transformation for estimating differences between proportions [15], where;

$$\begin{array}{c} \varphi =2\;\text{arcsine}\left(\sqrt{\text{p}}\right)\\ \text{h}=\left|\varphi_{1}-\varphi_{2}\right| \end{array}$$

P is the proportion and h is the effect size to be detected. The best available estimate of the population proportion currently active at the recommended level was that taken from Active People Survey 2 [16] (sub-group NS-SEC 6-8 i.e. those most closely matching the demographic profile of the target population for this study), which was 7.5%. Based on our previous research [17], we anticipate being able to achieve a 10% increase in this population proportion i.e. 17.5% after the community-led intervention. Using Cohen's arcsine formula this gives a standardised effect size of 0.273. Assuming a false positive error rate of .05, statistical power of .8 and this standardised effect size, we have calculated a required sample size of 283 participants at follow-up. Further, assuming a survey response rate of 10% (expected to be low for this target population) the issued sample size will be 2830 surveys.

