### Phase II: Establish working Groups for intervention planning

Each ward of Stoke-on-Trent, UK has an Area Implementation Team (AIT) which is directly aligned to Stoke-on-Trent City Council, Stoke Primary Care Trust, and the Local Strategic Partnership and involves membership from joint services (e.g. Health, Police and Fire Services, private, community and voluntary sector organisations). The aim here is to bring both the target community and a multidisciplinary professional perspective to the process of planning the intervention. Encouraging individuals and groups for whom the intervention is intended will help optimise sustainable consensus and action. This will be achieved through the AIT network by the formation of neighbourhood "Working Groups" with representation from those who are the intended beneficiaries and those implementing the programme taking account of the need for culturally relevant programmes for diverse groups. Community participants are likely to be a mixture of unaffiliated residents, voluntary organizations, staff members from the AIT and leaders from community organizations. It is recognized that over time membership of these groups may change. The task of these groups will be to help determine performance objectives and determinants to develop an overall matrix of change objective grid; this process is described in Phase III. The AIT Network will help with the setting up and coordination of these groups and a dedicated Community Development Worker (CDW) will be allocated to each area. These CDWs will act as agents and catalysts for change and will work across several levels and will be responsible for increasing motivation and demand for health. This will be achieved through an approach which combines community engagement with supportive policy change that focuses on facilitating and creating healthy urban environments (as identified by community members themselves).

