### Data analysis

Chi-squared analysis will be used to test for differences in the distributions of PA categories in the intervention and control areas. Multinomial logistic regression analysis will be used to derive odds ratios for the various physical activity categories between the areas. Qualitative analysis of the interviews and discussion groups will follow the principles of thematic analysis [30]. The interviews will be audio tape-recorded, transcribed and entered onto a database. Then using the qualitative analysis computer package N-Vivo it is planned to conduct a thorough coding of the data followed by identification of basic themes and larger themes.

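### The sample size and the named tests treat residents as independent although three whole wards receive the intervention and are compared with other wards, so the nominal 5% error rate does not hold once outcomes correlate within wards

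*Protocol article*

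**What the plan says.** **Delivery is by area.** Study design describes a pre-post case study in three electoral wards whose targeted communities take part together. Phase II says that each ward has its own Area Implementation Team and that "a dedicated Community Development Worker (CDW) will be allocated to each area". Under Phase III, local working groups set their own priorities, so what is done may differ between wards.

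**The comparison is by area.** Primary outcome measures sets the change in physical activity in the three areas against the other wards of the city, using a national survey for the comparison.

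**The sample size is by individual.** Proposed sample size states: "Sample size calculations for the independent survey sample are based on Cohen's arcsine transformation for estimating differences between proportions". It goes on: "Assuming a false positive error rate of .05, statistical power of .8 and this standardised effect size", and then "we have calculated a required sample size of 283 participants at follow-up". The only inflation is for a 10% response rate.

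**The analysis is by individual.** Data analysis names a chi-squared test of activity categories between intervention and control areas, and adds: "Multinomial logistic regression analysis will be used to derive odds ratios for the various physical activity categories between the areas". It mentions no ward-level variance. Community survey promises inverse-probability weights for choosing one adult per address. Those weights do not deal with correlation within wards.

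**What is claimed.** Study aims says: "The aim of our proposed study is to determine the efficacy of a community-led intervention". Community survey says that power is sufficient for the expected difference, and Phase III says that programme elements were, where possible, designed with sufficient power.

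**The concern.** People in one ward share the worker, the team, the chosen activities and the neighbourhood. The article's own Background argues that neighbourhood conditions shape activity, which is a reason to expect correlated outcomes. A resident-level test takes its standard error from the number of respondents, whereas the uncertainty of a comparison between wards depends largely on how many wards there are and how much they vary. With three intervention wards, ordinary variation between wards, or in ward trends, can be declared an effect.

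The main risk is a false go-ahead. Study aims and the Abstract say that positive findings would lead to a larger controlled trial, which the Abstract describes as cluster randomised. A p-value that is too small and an interval that is too narrow would feed that decision.

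**Working it through.** **1. The plan's own figure.** Inputs from Proposed sample size are alpha 0.05, power 0.80, baseline 7.5%, and "we anticipate being able to achieve a 10% increase in this population proportion i.e. 17.5% after the community-led intervention". The article then says: "Using Cohen's arcsine formula this gives a standardised effect size of 0.273".

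- Arcsine formula on 7.5% and 17.5%: h = 2·arcsin(√0.175) − 2·arcsin(√0.075) = 0.308, not 0.273.
- n per group = 2(1.96 + 0.842)²/h². This gives 211 at h = 0.273 (421 in total before rounding up) and 165 at h = 0.308 (330 in total).
- One-sided at h = 0.273: 166 per group.
- The stated 283 is not reproduced. It is close to 90% power, two-sided, at h = 0.273 (282 per group).

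These mismatches are a separate matter. They count here because they make the power consequence depend on how 283 is read. No ICC, design effect or number of wards enters the formula.

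**2. Design effect and true type I error.** Respondents per ward, if split equally: m = 283/3 = 94.3. The article gives no ICC, so 0.005 to 0.02 is an assumed range.

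- Design effect: DE = 1 + (m − 1)·ICC
- Effective n = 283/DE
- True two-sided error of the unadjusted 5% test = 2[1 − Φ(1.96/√DE)]

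| ICC | DE | Effective n | True type I error |
|---|---|---|---|
| 0.005 | 1.47 | 193 | 10.6% |
| 0.01 | 1.93 | 146 | 15.9% |
| 0.02 | 2.87 | 99 | 24.7% |

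A beta-binomial simulation (94 per ward, 7.5% active, three wards against three) gave 10.6%, 15.8% and 25.0%. Three wards against an assumed 17 gave 10.4%, 15.3% and 24.5%.

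The value m = 94 takes all 283 as follow-up respondents in the three study wards, where the survey is run. If 283 covered both groups, m = 141.5/3 = 47.2. DE would then be 1.23, 1.46 and 1.92, and the error 7.7%, 10.5% and 15.8%.

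**3. Power.** With n per group, the same DE assumed on both sides and the variance corrected, power = Φ(h·√(n/(2·DE)) − 1.96). For example, at ICC 0.01 and h = 0.273: 0.273·√(283/(2·1.933)) = 2.336, and Φ(0.376) = 65%.

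| ICC | 283 per group, h = 0.273 | 283 per group, h = 0.308 |
|---|---|---|
| 0 | 90% | 96% |
| 0.005 | 77% | 86% |
| 0.01 | 65% | 75% |
| 0.02 | 48% | 58% |

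If 283 is the total, power is 63% (h = 0.273) or 74% (h = 0.308) before any clustering.

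These figures use a normal reference. With a t reference on 4 degrees of freedom (three wards against three, assumed) and 283 per group at h = 0.273, power is 68% at ICC 0, then 53%, 43% and 31%.

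**4. Limit set by three wards.** However many people are surveyed, effective n in three wards cannot exceed 3/ICC. The 211 needed at h = 0.273 is out of reach once the ICC exceeds 3/211 = 0.014.

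**The case against.** **This is a condensed article about a pilot.** Variance estimation is commonly left to a fuller plan, Background calls the study a pilot, and the Abstract leaves effectiveness to a later trial. That does not remove the point. The article itself fixes the formula, error rate, power and tests, claims sufficient power, and states an efficacy aim and a directional hypothesis. Pilot status does weaken the consequence: ignoring clustering affects the standard error rather than the expected point estimate, so the main harm is a false go-ahead, not a biased effect size.

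**Stable ward differences cancel in a pre-post contrast.** This stands. For change over time the relevant ICC is the ward-by-time component, which may be smaller than a cross-sectional ICC. Re-issuing the survey to wave 1 respondents also makes an independent-samples test of change conservative, which partly offsets clustering. The percentages above are therefore a range under assumption, not an estimate for this study.

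**Stronger readings that a reader might infer.**

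- *The 80% power is simply not delivered.* The documents do not support this without conditions. With 283 per group, h = 0.308 and a normal reference, power is still 86% at ICC 0.005. The 80% line is crossed at an ICC of about 0.004 for h = 0.273 and about 0.008 for h = 0.308.
- *The named tests are invalid on weighted data.* Data analysis does not say that the tests are unweighted or unadjusted for the survey design. A Rao-Scott test is also a chi-squared test and would fit the wording.
- *Clustering by Lower Super Output Area can be quantified too.* Dividing the roughly 10,000 adults in Study design by the roughly 1,500 residents per area in Study population mixes adults with total population. Sampling addresses within each such area also reads as stratification.

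**Conclusion.** The concern holds for the comparison that the article makes primary. Delivery and comparison are at ward level, while the sample size and the named tests are at resident level with no allowance for ward-level variation. Any positive ICC on the contrast analysed takes the unadjusted test above its nominal 5%, apart from the partial offset from repeat respondents in a contrast of change. At 94 respondents per ward and assumed ICCs of 0.005, 0.01 and 0.02, the size is about 10.6%, 15.9% and 24.7%.

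The power loss is conditional on the ICC, on which h applies, on the meaning of 283 and on the reference distribution. It should be reported as a range. More respondents per ward cannot overcome having only three intervention wards.

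**What to change.** **Data analysis**

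- Base the comparison with the other wards on ward-level inference: ward-level summaries of change, or a weighted model with ward as random effect or cluster. Use small-sample degrees of freedom.
- Do not put ward fixed effects in that contrast, because they would absorb the intervention term.
- For the before-after contrast within the intervention areas, use survey-weighted tests (for example Rao-Scott) that account for people who answer at both waves.
- Show the three ward-level changes separately.

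**Proposed sample size**

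- Say whether 283 is per group or a total.
- Replace the 80% claim with power under a design effect over a stated ICC range.

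**Reporting**

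- Give the ICC with its interval, which the later cluster-randomised trial will need. With so few wards the interval will be wide.
- Present the result as a preliminary estimate with a confidence interval, not as a test of efficacy.

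**Cost.** Changes of wording and some further analysis, wider intervals and a less favourable power figure. None of this removes the limit that three wards place on inference.

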### Ethical arrangements

Ethical approval has been obtained by the Research Ethics Committee, Staffordshire University.

## Discussion

The need for a community-led collaborative approach to combating social inequalities in health has grown out of the recognition that many of the complex determinants of health lie beyond the control of the individual and even of clinical and public health institutions alone. Social factors have a strong influence on health and longevity. Those in deprived areas often lack access to health services, which reduces their likelihood of having disease detected early, live in areas where there is poor access to fresh affordable food and areas to play and participate in physical activities (green space areas run down, vandalised) and often have a number of lifestyle modifiable risk factors (e.g. smoking, sedentary behaviour, high alcohol intake) that compound these health issues. In addition, those living in poor areas are more likely to suffer from depression, stress and poor mental health [31,32].

There is a need to develop evidence-based practice around health interventions that improve public health of communities. Development of an evaluation framework and dissemination of best practice would add considerably to the current evidence-base and offer possibilities for future service innovation across other NHS PCTs.

## Conclusions

There is a need to develop new approaches to combating health inequalities. A community-led approach is an important component of health improvement policy and practice. However, although these approaches are often described, their impact is seldom evaluated and the process of integrating into local area planning usually ignored. Community participatory research and community-led intervention are grounded in the concepts of "local community" and "local control" and in combination may potentially provide the required social and political combination to address some of the health inequalities related to physical activity.
